**Fig. 3 Fig3:**
[figure not shown]
Fingertip unit measurement

### Experimental medicine (*Jaungo*)

*Jaungo* ointment (Hanpoong Pharm and Foods, Co., Ltd., Wanju, Korea) was produced according to Korea Good Manufacturing Practice standards. *Jaungo* was approved for the treatment of xerosis cutis, frostbite, miliaria, anal fissure, and rhus dermatitis on 11 September 2014, by the KFDA. It is licensed to be applied to skin lesions one or more times per day.

*Jaungo* is composed of two herbs and three carrier oils: 72.7 mg of *Lithospermi* radix, 60.6 mg of *Angelica gigantis* radix, 60.1 mg of sesame seed oil, 242.4 mg of bees wax, and 18.2 mg of swine oil based on a total 1 g of ointment. It is a red-colored ointment with an herbal fragrance. The characteristic red color is due to the *Lithospermi* radix, and the distinctive aroma is due to the flavor components of bees wax and *Angelica gigantis* radix.

### Placebo medicine

Hanpoong Pharm and Foods Co., Ltd., developed a homogenous ointment that is red in color with an herbal fragrance made with 698.1 mg sesame seed oil, 279.2 mg bees wax, 21 mg swine oil, 1.2 mg red iron oxide, and 0.5 mg ginseng-flavored extract based on a total 1 g of ointment. Substances, content, and preparative methods of the placebo ointment were approved by KFDA. The placebo ointment is very similar to the experimental medicine *Jaungo* in color, form, weight, and odor.

### Intervention discontinuation

Participants may discontinue the trial in the following cases: violation of the inclusion/exclusion criteria, violation of combinational medications, the occurrence of serious adverse events, request by participant due to side effects, determination by the investigator due to side effects, systematic disease discovered during the trial, request of participant or their guardian to discontinue, the need for surgery or hospitalization due to accidents or diseases, pregnancy, worsening of atopic dermatitis, continuation judged inappropriate by the investigator.

### Early closure

If participant AD symptoms disappear, the investigator may terminate the case early after discussion with the sponsors and the statistician.

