## Outcomes

### Primary outcome measurement

The primary outcome will be measured by changes in the Eczema Area and Severity Index (EASI) before and after 3 weeks’ application of experimental medications. Key signs of eczema, including erythema (E), infiltration/population (I), excoriation (Ex), and lichenification (L), will be assessed on a numeric scale of 0 to 3. Then, the percentage of area involved for each of the four body regions will be assigned a proportional score from 0 to 6: 0 = no eruption; 1 = <10%; 2 = <10–29%; 3 = <30–49%; 4 = <50–69%; 5 = <70–89%; and 6 = >90–100%. Finally, an established multiplier based on the age of the patient will be used. Please refer to the following formula for patients over 8 years of age. The multiplier for patients under 8 years of age is indicated in parentheses and in italics:

Upper Limbs [(E + I + Ex + L) × Area × 0.2 (*0.2*)] + Lower Limbs [(E + I + Ex + L) × Area × 0.4 (*0.3*)] + Trunk Limbs [(E + I + Ex + L) × Area × 0.3 (*0.3*)] + Head/Neck [(E + I + Ex + L) × Area × 0.1 (*0.2*)] [11].

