### Safety outcome measurements

Prior to randomization and immediately after treatment completion, we will perform the following tests on all participants: CBC D/C, AST/ALT, BUN/Cr, ESR, and vital signs. These tests will serve to exclude participants who have serious illnesses or abnormal liver, kidney, or other organ function. Additionally, subjective dermal tolerability assessment and the Draize score will be assessed after completion of the study [16].

Listed adverse events verified by the KFDA for *Jaungo* include allergic skin reactions including rash and pruritus. Investigators will assess the incidence and intensity of adverse events. In addition, a causality evaluation of adverse drug reactions will be discussed and documented in Case Report Forms.

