### Blinding

To ensure blinding, a matched placebo ointment identical in color, texture, weight, and odor will be utilized and stored in a container identical to that of *Jaungo*. The *Jaungo* and placebo ointments will be labeled with a random number and “for morning use” or “for evening use” in an identical form. Treatment group 1 will receive two containers of *Jaungo*, one labeled with “for morning use” and the other “for evening use,” treatment group 2 will receive one container of *Jaungo* and one container of placebo ointment where one of the containers is labeled with “for morning use” and the other “for evening use.” The placebo group will receive two containers of placebo ointment, one labeled with “for morning use” and the other “for evening use.” The clinical pharmacist will supply *Jaungo*, the placebo ointment, or both to the patient depending on the patient’s assigned number. If the ointments are lost or destroyed, the clinical pharmacist will supply the patient with extra ointment labeled in an identical manner to maintain blinding.

In this trial, treatment distribution will remain unknown to the participants, investigators, outcomes assessors, statistician, and other staff until the end of the study. The randomization list and blinding codes will be kept strictly confidential. Access to the randomization list will be limited to the Clinical Research Organization (CRO) staff and the list will only be opened as a standard operating procedure. In the event that the randomization list has to be opened immediately, owing to an urgent situation pertaining to serious adverse events, the primary investigator must report the incident to the CRO. Participants will remain blinded to their respective treatment group until the final visit of the last randomized participant. The success of blinding will be assessed at each participant’s final visit. Researchers who are blinded to the distribution data will perform the outcome assessment. The blinding procedure will also be verified by the authorized CRO.

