### Statistical analysis

The primary hypothesis is that topical application of *Jaungo* is more effective than the placebo ointment for treating AD. Baseline data collected on each participant at randomization in the trial will be used to describe the population of patients, assess comparability of treatment groups, achieve balanced randomization, adjust for possible confounding prognostic factors, and undertake subgroup analyses. The baseline characteristics of the three groups, including sex, age, duration of AD, total IgE level, and SCORAD score will be compared. Analysis of variance (ANOVA) will be used to investigate differences in continuously scaled variables, and chi-squared tests will be used to identify significant variations in proportions across treatment groups.

We will also compare the efficacy of *Jaungo* and placebo ointments based on the change in primary outcome, or EASI score, from day 0 to the end of the study period (3 weeks). Mean differences in the EASI score from baseline value to the end of treatment will be compared using ANOVA among the three groups. A paired Student’s *t* test will be used to compare the mean change within a group. Secondary outcomes (SCORAD score, TEWL, DLQI, total IgE, eosinophil count, IL-17, IL-22, and IFN-γ) will also be utilized to compare the efficacy of *Jaungo* and placebo ointments in the same manner as the primary outcome/EASI score. To evaluate safety, the Draize score and adverse events will be presented in a descriptive manner.

Analyses will be performed for two populations: (1) an intention-to-treat population consisting of all randomized participants who have at least one measurable outcome to report following treatment (missing data are replaced with the last observation values) and (2) a per-protocol population including only participants without major protocol deviations. All data will be descriptively analyzed. All main analyses will be based on the intention-to-treat population and conducted using the last observation carried forward imputation method. Statistical analyses will be conducted in a blind manner by an independent statistician and performed using the SPSS 21 (IBM Inc., Armonk, NY, USA), where the level of significance is established at *α* = 0.05.

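### Early closure on clearance can end a participant's case before week 3, and nothing shown keeps the week-3 EASI that defines the primary endpoint

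*Protocol article*

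**What the plan says.** All references are to the protocol article.

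- **Early closure:** "If participant AD symptoms disappear, the investigator may terminate the case early after discussion with the sponsors and the statistician". The trigger is disappearance of symptoms, with no threshold given. What ends is the participant's case, not only the ointment.
- **Primary outcome measurement:** "The primary outcome will be measured by changes in the Eczema Area and Severity Index (EASI) before and after 3 weeks" of application.
- **Statistical analysis, time point:** the change is first described as running "from day 0 to the end of the study period (3 weeks"), and the next sentence says "Mean differences in the EASI score from baseline value to the end of treatment will be compared using ANOVA among the three groups".
- **Statistical analysis, missing data and population:** the intention-to-treat set is "all randomized participants who have at least one measurable outcome to report following treatment", and "missing data are replaced with the last observation values", that is, last observation carried forward (LOCF).
- **Safety outcome measurements:** "Prior to randomization and immediately after treatment completion, we will perform the following tests on all participants". This covers laboratory tests and vital signs and does not name EASI.
- **Blinding:** "treatment distribution will remain unknown to the participants, investigators, outcomes assessors, statistician, and other staff until the end of the study".
- **Randomization and allocation:** 34 participants, 1:1:1, with 11–12 per group.

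**The concern.** The rule lets follow-up end because of a good result. The participants who may lack a week-3 EASI are therefore the best responders, and whether they lack it depends on their outcome and on the investigator's discretion. The two descriptions of the primary time point agree for anyone treated for the full 3 weeks. They differ for someone closed early, which is the group this rule creates.

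LOCF supplies a number for week 3 but does not observe one. Carrying a cleared score forward assumes that clearance lasts after the ointment stops, although the Background section describes a disease that needs long-term care to prevent flares. With 11–12 per arm, one participant carries 1/12 = 8.3% to 1/11 = 9.1% of an arm mean, so one or two such cases are visible in the primary comparison. A later analysis plan can choose an imputation, but it cannot recover a score that was never taken.

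**Working it through.** The plan gives no figure on this point to reproduce: no effect size, SD, baseline EASI or closure rate. The check has two parts: what the text leads to for a closed participant, and how large the error could be on assumed values.

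**What the text leads to.** The article describes randomization at visit 2, container return at visit 3, and outcomes measured before and after 3 weeks of application. It describes no efficacy assessment in between. Three results are possible for a participant closed on clearance:

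- **(a)** A cleared EASI is taken at closure and carried to week 3. This is the most plausible, since safety tests are due when treatment ends and judging clearance needs a skin examination.
- **(b)** No EASI is taken at closure, some other post-treatment outcome exists, and the baseline EASI is carried forward. The responder is scored as unchanged.
- **(c)** No post-treatment outcome is recorded, and the responder leaves the intention-to-treat set.

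**Inputs.** From the document: n = 11 per arm (12 as a check). Assumed, for illustration only: k1 and k0 closures in an active and the placebo arm; baseline EASI b = 4 to 8 in closed participants; full clearance at closure; relapse r = 1 to 3 points by day 21 in every closed participant; all others improve by m = 2 points in both arms.

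**Formulas.** Error = observed minus true between-arm difference in mean improvement. A closed participant's true week-3 improvement is b − r.

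- (a) scored b: error = (k1 − k0) × r / n
- (b) scored 0: error = −(k1 − k0) × (b − r) / n
- (c) dropped, so both observed means equal m: error = −(k1 − k0) × (b − r − m) / n

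**Results for k1 = 2, k0 = 1, n = 11 (EASI points).**

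| b | r | (a) | (b) | (c) |
|---|---|---|---|---|
| 6 | 1.5 | 1.5/11 = +0.14 | −4.5/11 = −0.41 | −2.5/11 = −0.23 |
| 4 | 1 | 1/11 = +0.09 | −3/11 = −0.27 | −1/11 = −0.09 |
| 4 | 3 | 3/11 = +0.27 | −1/11 = −0.09 | +1/11 = +0.09 |
| 8 | 1 | 1/11 = +0.09 | −7/11 = −0.64 | −5/11 = −0.45 |
| 8 | 3 | 3/11 = +0.27 | −5/11 = −0.45 | −3/11 = −0.27 |

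**Sensitivity.**

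- k1 = 1, k0 = 2: same sizes, opposite signs.
- k1 = k0 with equal relapse: 0 in all three.
- k1 = k0 = 1 with relapse of 1 point on active and 3 on placebo: (a) is (1 − 3)/11 = −0.18.
- No relapse: (a) is 0 whatever the closures.
- n = 12, base case (b = 6, r = 1.5): (a) is 1.5/12 = +0.13.

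**The case against.** The strongest objection is that this is a condensed article. Procedures for an early-termination visit normally sit in the full protocol, and the schedule figure is not shown, so a closure EASI or a week-3 visit may already be required. The shown text also points to a closing assessment, through safety tests on all participants and a blinding check at each final visit. On that reading (b) and (c), which give the largest numbers, are remote. In (a), LOCF is an explicit prespecified rule. Closures may be few in 3 weeks among patients selected for lichenification, excoriation and dryness. Closure also requires discussion with the sponsors and the statistician, and the investigator and statistician are blinded. Finally, an off-treatment week-3 score is not strictly the effect of 3 weeks' application either, so the choice may be one of estimand.

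Most of this stands and limits the weight of the point. Blinding means closure does not follow known allocation, and consultation is a check on casual use. Every magnitude above is assumed, and a relapse of 3 points from a baseline of 4 is severe. Two things remain. The closure rule is stated text, not an omission, and applied as written with LOCF it carries a cleared score past any relapse. And the matter is more than a preference between estimands: with an EASI at the stop and another at week 3 both quantities are observed, whereas closing the case forgoes one of them.

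**Conclusion.** The concern holds as a minor point. The article permits a case to end on a favourable outcome, sets the primary endpoint at week 3, and shows nothing that keeps the week-3 EASI for those participants.

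No direction of bias can be claimed: it depends on which arm has more closures or more relapse. For the most plausible result, (a), the illustrative error is 0.09 to 0.27 EASI points in either direction when closures differ by one. It vanishes if clearance persists, or if closures and relapse are equal across arms. These sizes rest on assumed closures, baseline, relapse and improvement in the others, and the real effect is probably modest. The conclusion is conditional on the full protocol and schedule not already requiring the visit.

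**What to change.** - **Early closure:** reword so that on clearance the ointment may be stopped and an EASI is taken at the stop. The participant stays in the trial and attends the scheduled week-3 visit for efficacy and safety. Record the stop date and exposure.
- **Statistical analysis:** name week 3 as the single time point of the primary change, in place of the end-of-treatment wording, and use the observed week-3 EASI for these participants. The EASI at the stop can support an additional end-of-treatment analysis.

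The cost is a rewording of one section, one phrase in another, and one EASI per early stop. The downside is that a few cleared participants keep a visit that was already planned, and their week-3 EASI is measured off treatment.

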### Adherence assessment

Adherence will be assessed by a container count at visit 3. Participants will bring in experimental medications at visit 3, more than 80% use of experimental medication will be defined as “good adherence,” and less than 80% use will be defined as “poor adherence.” Because the amount of ointment applied by each participant will be different according to the extent of the involved lesion, adherence will be calculated according to the dose of ointment distributed for each participant.

### Combination medications

Different medications for AD, such as orally administered antihistamines, GCs, and immunosuppressants, will not be allowed throughout the study period; however, after discussion with the investigators, patients can self-administer antihistamines orally for controlling pruritus. Patients will also be allowed to use emollients, lotions, and ointments that do not contain GCs during the study. Additional herbal prescriptions, acupuncture treatments, or therapeutic interventions by other clinicians will not be allowed during the study period.

These restrictions are based on the information provided by the patient, and researchers will have to evaluate whether the information provided will affect AD. Drugs taken by each participant will be recorded at every visit, and participants will be asked to notify us of any changes in their medication/supplement regimen. If the participant received medications that may affect AD, they will be excluded from the study.

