### Randomization and allocation

Before assigning randomization, all participants will be informed that they will be distributed into one of three groups. Thirty-four participants will be randomized into three groups in a 1:1:1 ratio, using block randomization with a block size of 3 or 6, where 11–12 participants are planned for each group. Randomization distribution will occur on the second visit to the clinical research center. Participants will be assigned random numbers via a web-based random number generator system developed by an independent expert on web programming using Django Web Framework (https://www.djangoproject.com). The clinical pharmacy will be supplied with the experimental and placebo ointments in identical containers labeled with random numbers, which correspond to the participant’s assigned number, and “for morning use” or “for evening use.” The participant’s randomly assigned number will dictate which ointments the clinical pharmacist will supply to them.

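### Excluding randomised participants from the study for taking AD medication can remove them from the main EASI analysis for a reason related to response

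*Protocol article*

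**What the plan says.** All references are to the protocol article.

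- **Combination medications:** the rule is "If the participant received medications that may affect AD, they will be excluded from the study". It is worded as mandatory, and the exclusion is from the study, not from study ointment or from one analysis set. The same section adds: "Drugs taken by each participant will be recorded at every visit, and participants will be asked to notify us of any changes".
- **Randomization and allocation:** "Randomization distribution will occur on the second visit to the clinical research center". The plan is 34 participants, 11 to 12 per group.
- **Primary outcome measurement:** "The primary outcome will be measured by changes in the Eczema Area and Severity Index (EASI) before and after 3 weeks" of application. The secondary outcomes have the same two time points.
- **Statistical analysis:** the main set is "an intention-to-treat population consisting of all randomized participants who have at least one measurable outcome to report following treatment", and "All main analyses will be based on the intention-to-treat population and conducted using the last observation carried forward imputation method". A second set is "a per-protocol population including only participants without major protocol deviations".
- **Intervention discontinuation:** a breach of the co-medication rules is listed as a ground on which a participant may discontinue. The list also includes "pregnancy, worsening of atopic dermatitis, continuation judged inappropriate by the investigator".

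**The concern.** A participant who turns to a topical steroid, an immunosuppressant or another clinician during the three weeks has probably not done well on the allocated ointment, or has reacted to it. The safety section lists rash and pruritus as known reactions to Jaungo. If such a participant is taken out of the study, the arm loses a result that is likely to be worse than average, and the comparison of randomised groups is no longer fully protected by randomisation. Blinding limits deliberate bias in judging which drugs count, but it does not prevent loss that depends on outcome.

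The estimates are meant to inform later confirmatory trials, and each arm has only 11 or 12 participants, so one or two such losses could be visible in an arm mean. A week-3 EASI that was never taken cannot be recovered at the analysis stage.

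**Working it through.** **1. Does the rule reach randomised participants?** Yes. Drugs taken before entry are dealt with in the exclusion criteria. The co-medication section concerns the study period and collects drug use at every visit, and randomisation is at visit 2.

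**2. What happens to an excluded participant in the main analysis?**

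| When use comes to light | EASI after treatment, on the stated schedule | Consequence |
|---|---|---|
| Before week 3, participant excluded | None stated | Does not meet the main set's condition of an outcome after treatment, so is lost from the main analysis |
| At visit 3 | Due at about that time | The co-medication sentence says exclude; the statistical analysis section would keep the participant and has a per-protocol set for major deviations |

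Last observation carried forward does not help in the first row, because the text states no EASI between day 0 and week 3 that could be carried.

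**3. How large could the effect be?** The article gives no SD, effect size, power, dropout or exclusion rate, so there is no figure of its own to reproduce here. The following is an illustration only.

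Assumptions: EASI change is normal with SD 1 (so results are in SD units), higher is worse, and the tendency to take medication has correlation ρ with the change. The participant with the greatest tendency is lost from one arm of n.

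The expected largest of n standard normal values is E₁ = 1.629 for n = 12 and 1.586 for n = 11. The shift in the arm mean is ρ × E₁ / (n − 1).

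| | ρ = 1 | ρ = 0.7 | ρ = 0.5 | ρ = 0 |
|---|---|---|---|---|
| n = 12: ρ × 1.629 / 11 | 0.148 | 0.104 | 0.074 | 0 |
| n = 11: ρ × 1.586 / 10 | 0.159 | 0.111 | 0.079 | 0 |

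The standard error of a two-arm difference at 12 per arm is √(2/12) = 0.408 SD. One loss is therefore 0.148 / 0.408 = 36% of a standard error at ρ = 1 and 0.074 / 0.408 = 18% at ρ = 0.5.

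For two losses from the same arm of 12, with second-largest expected value 1.116, the shift at ρ = 1 is (1.629 + 1.116) / 10 = 0.27 SD, and half that (0.14 SD) at ρ = 0.5. A simulation of 400,000 runs at n = 12 gave the same values for one and two losses.

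**4. Which way would it go?** Losing poor responders from placebo makes placebo look better and shrinks a Jaungo advantage. Losing them from a Jaungo arm inflates it. Similar losses in all arms would largely cancel.

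**The case against.** The strongest reply is that the co-medication sentence is only loose wording for the discontinuation rule, and that the statistical analysis section governs who is analysed. That section has no medication exclusion from the main set and removes deviators only from the per-protocol set. For use found at visit 3 this reading is reasonable. A reader might infer that such participants are certain to be dropped despite having a week-3 EASI, but the text does not establish that. What remains is wording that points the other way and should be brought into line.

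The reply is weaker for exclusion before week 3. The visit schedule (Fig. 2) is not shown and may contain an EASI at early withdrawal, which would reduce the loss. Early detection may also be uncommon: ointment is returned at visit 3, which looks like the end of treatment, so earlier exclusion would mostly depend on participants reporting between visits. Emollients are allowed, as are antihistamines after discussion; the disease is mild to moderate and treatment lasts three weeks. All of this supports expecting few exclusions. It does not change what the stated rules do when an exclusion happens.

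A reader might also infer that excluded participants would enter the main set with the day-0 EASI carried forward, and so be scored as unchanged. The documents do not support this. It would need some other outcome after treatment but before week 3, and none is named: the secondary outcomes share the EASI time points and the safety tests follow treatment completion.

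Finally, the proposed follow-up does not restore the change that would have been seen without rescue. A participant who used a steroid contributes a steroid-affected week-3 EASI. That is correct, and including or setting aside rescue use is partly a choice of what to estimate. It is a reason to add a sensitivity analysis, not to leave outcomes uncollected.

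**Conclusion.** The point stands in a limited form. The article itself fixes the exclusion rule, the assessment times and the condition for the main set. Together they allow a randomised participant to be lost from the main EASI analysis for a reason plausibly linked to response. This is a rule that is badly fixed, not merely detail left to another document.

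A reader might go further and infer a bias in favour of Jaungo. Nothing in the documents supports a direction: it depends on which arm loses participants, and no exclusion rate is given. The 0.15 SD for one loss from an arm of 12 assumes normal changes, loss from one arm only and perfect correlation between medication use and outcome. It falls to zero if use is unrelated to outcome, and even at its extreme it is well below the 0.41 SD standard error.

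Given the exploratory phase IIa design, severity is minor to moderate. Confidence is medium, because the assessment schedule is not visible.

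**What to change.** Replace the sentence with wording such as:

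> Participants who take prohibited AD medication may stop study ointment but remain in follow-up, have EASI when this is identified if feasible and at week 3, and are analysed in their randomised arm; prohibited medication leads to exclusion from the per-protocol population only.

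Report prohibited medication use by arm, and add a sensitivity analysis that uses the EASI at or before rescue. Where use emerges only at visit 3, the only earlier EASI in the stated schedule is day 0, so this analysis will say little about that participant.

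The cost is a short amendment, likely to need ethics and regulator review because the protocol is approved and enrolment has begun. It needs no extra participants and no visits beyond the planned week-3 visit, apart from an EASI when use is identified. The main estimate will include the effect of any added medication, so the per-protocol and sensitivity results should be shown beside it.
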